## Abstract

**Background:**

The Coping with Persistent Pain, Effectiveness Research into Self-management (COPERS) trial assessed whether a group-based self-management course is effective in reducing pain-related disability in participants with chronic musculoskeletal pain. This article describes the statistical analysis plan for the COPERS trial.

**Methods and design:**

COPERS was a pragmatic, multicentre, unmasked, parallel group, randomised controlled trial. This article describes (a) the overall analysis principles (including which participants will be included in each analysis, how results will be presented, which covariates will be adjusted for, and how we will account for clustering in the intervention group); (b) the primary and secondary outcomes, and how each outcome will be analysed; (c) sensitivity analyses; (d) subgroup analyses; and (e) adherence-adjusted analyses.

**Trial registration:**

ISRCTN24426731

## Update

### Background

COPERS (Coping with Persistent Pain, Effectiveness Research into Self-management) was a pragmatic, multicentre, unmasked, parallel group, randomised controlled trial [1]. The protocol for the COPERS trial has been published previously [1] and gives details on the rational for the trial, the intervention and control groups, the inclusion/exclusion criteria, and the sample size calculation. Briefly, the main aim of the COPERS trial was to assess whether a group-based learning course was effective in reducing pain-related disability in participants with chronic musculoskeletal pain [2]. The intervention was a 3-day training course. Course content is shown in Table 1, and the schedule of assessments is shown in Figure 1. The intervention was compared with usual care plus a relaxation CD and pain education leaflet. In this article, we describe the statistical analysis plan, which outlines how data analysis for the COPERS trial will be performed.

The statistical analysis plan was finalised and approved on 3 October 2013. All trial investigators were blinded to patient outcomes broken down by treatment group until after the analysis plan was signed off and the database was locked. Participant recruitment began in August 2011 and finished in July 2012 (participant follow-up was completed in August 2013). The trial database was locked after the statistical analysis plan was approved. Data analysis did not begin until after the analysis plan was approved, and after the database was locked.

**Figure 1 F1:**
[figure not shown]
**Schedule of assessment.** CPG, Chronic Pain Grade (Von Korff [3]); HADS, Hospital Anxiety and Depression Scale (Zigmond and Snaith [5]); EQ-5D, Quality of life (EuroQol.org); PSEQ, Pain Self-Efficacy Questionnaire (Nicholas 1989, [4]); CPAQ, Chronic Pain Acceptance Questionnaire (McCracken [6]); HEIQ, Social integration [7]; Census global health question (ons.gov.uk/census/2011-census).

**Table 1 T1:** The Coping with Persistent Pain, Effectiveness Research into Self-management (COPERS) course content overview

**Day (10.00 am to 2.45 pm)**	**Modules**
**Day 1**	Introduction and understanding pain and acceptance
Living and dealing with pain	
	Lunch
	Activity: Art
	Mind, mood and pain
	Movement and posture, and Relaxation
**Day 2**	Dealing with unhelpful, negative thoughts and barriers to change
Doing something about your life with pain	
	Lunch
	Activity: Hand massage
	Making pain more manageable
	Movement and Relaxation
**Day 3**	Communication skills
Communication and relationships	Lunch
	Activity: Volunteering
	Movement and Relaxation
**Day 4**	The future
Follow-up (2 weeks later, 10.00 am to 12.00)	

The original sample size calculation called for 685 participants (391 in the intervention group and 294 in the control group, to be randomised in a 4:3 ratio). However, we required a sufficient number of participants in each group-based learning course to make the intervention viable; therefore, we continued recruitment until there was an adequate number of participants for each course. This led to 703 participants (403 intervention, 300 control).

Ethics approval was granted by Cambridgeshire Ethics 11/EE/04. All patients provided written informed consent prior to randomisation.

### Outcomes

#### Primary outcome

The primary outcome was the pain-related disability score (which is a subscale of the Chronic Pain Grade questionnaire (CPG disability) [3]) at 12 months post-randomisation.

The three questions in this subscale assess the extent to which the participant’s pain has, in the previous 6 months: (i) interfered with their ability to perform their daily activities; (ii) changed their ability to take part in recreational, social, and family activities; and (iii) changed their ability to work. Each of the three questions is rated on a scale of 0 to 10, with 0 reflecting no change or interference, and 10 reflecting extreme change or interference.

The primary outcome is the mean of these three questions, multiplied by 10; that is, if X1, *X*2, and X3 represent the three questions, and Y represents the primary outcome, then:

$$Y=10*\left(X1+X2+X3\right)/3$$

The primary outcome is therefore recorded on a scale from 0 to 100, with higher scores reflecting larger interference or change in the participant’s ability to perform daily activities, work, or take part in recreational, social, and family activities.

#### Secondary outcomes

The secondary outcomes are:

1. CPG disability at 6 months post-randomisation [3]

2. CPG pain intensity score at 6 and 12 months post-randomisation [3]

3. Pain Self-Efficacy Questionnaire (PSEQ) score at 6 and 12 months post-randomisation [4]

4. Hospital Anxiety and Depression Scale (HADS) Anxiety score at 6 and 12 months post-randomisation [5]

5. Hospital Anxiety and Depression Scale (HADS) Depression score at 6 and 12 months post-randomisation [5]

6. Chronic Pain Acceptance Questionnaire (CPAQ) score at 6 and 12 months post-randomisation [6]

7. Health Education Impact Questionnaire (HEIQ) Social integration score at 6 and 12 months post-randomisation [7]

8. EQ-5D at 6 and 12 months post-randomisation [8]

9. Census global health question at 6 and 12 months post-randomisation [9]

10. Total Defined Daily Doses (Total DDD) of psychotropic drugs consumed up to 12 months post-randomisation

11. Total DDD of analgesics (including all opioids and other central nervous system drugs) consumed for pain up to 12 months post-randomisation

12. Total DDD of weak opioids consumed up to 12 months post-randomisation

13. Total DDD of strong opioids consumed up to 12 months post-randomisation

14. Proportion of participants using weak opioids at 12 months post-randomisation (defined as having received a prescription for a weak opioid up to twelve weeks before the 12-month follow-up date)

15. Proportion of participants using strong opioids at 12 months post-randomisation (defined as having received a prescription for a strong opioid up to twelve weeks before the 12-month follow-up date)

A guide to how outcomes are derived is available in Additional file 1.

### Analysis principles

#### General analysis principles

The main analysis for each outcome will use intention-to-treat (ITT) principles, meaning that all participants with a recorded outcome will be included in the analysis, and will be analysed according to the treatment group to which they were randomised [10]. More information on which participants will be included in each analysis is available in later sections. All *P* values will be two sided, and the significance level is set at 5%.

Analyses for all outcomes will be presented as:

1. The number of participants included in the analysis, by treatment group;

2. A summary measure of the outcome, by treatment group (for example, mean (SD) for continuous outcomes, number (%) for binary outcomes). Only participants with a completely recorded outcome will be used to calculate the summary measure (for example, participants who complete only one of three components of the CPG disability score will not be included in the calculation of the summary measure, although they will be included in estimated the treatment through the use of multiple imputation - see later sections);

3. A treatment effect, with a 95% confidence interval;

4. A two-sided *P* value.

All analyses will account for clustering by course in the intervention group. This is because when the intervention is delivered in clusters (for example, in a group setting, or when the same therapist treats multiple patients) it is necessary to account for the clustering in the analysis to avoid increasing the type I error rate [11-13]. Participants in the control group (who do not attend courses), will act as their own cluster (that is, each participant in the control group will belong to a 'course’ where they are the only member).

Site of recruitment (London or Midlands) [14-17], age, gender, and the HADS depression score at baseline will be included as covariates in each analysis [17-20]. Additionally, for continuous outcomes (CPG disability, CPG pain intensity, PSEQ, HADS Anxiety, HADS Depression, CPAQ, HEIQ, and EQ-5D), the outcome measured at baseline will be included in the analysis [19]. Site of recruitment will be adjusted for because it was used as a stratification factor in the randomisation process, and therefore, it is necessary to include it in the analysis to maintain correct type I error rates [11,14-16]. The other covariates will be included in the analysis because adjustment for prognostic factors can substantially increase power [17-21].

Continuous covariates (age, HADS depression score, outcome measured at baseline) will be analysed using a linear relationship with the outcome, as categorising continuous covariates has been shown to lead to poor performance in other scenarios [22]. We made the decision to assume a linear relationship prior to examining the observed association between covariate and outcome in the trial data, as previous research has shown that choosing the analysis method based on study data can lead to biased treatment effect estimates and incorrect type I error rates in some scenarios [23-27].

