### Analysis of primary outcome

The primary outcome (CPG disability at 12 months) will be analysed using a mixed-effects linear regression model, with a 'group-based learning course’ as a random effect. Restricted maximum likelihood (REML) will be used. The model will include site of recruitment, age, gender, HADS depression score, and CPG disability at baseline as covariates.

All participants who completed at least one of the three questions that form the CPG disability score at either 6 or 12 months will be included in the analysis. Participants who did not fill out any portion of the CPG disability score at both 6 or 12 months will be excluded from the analysis.

Multiple imputation (MI) [28] will be used to account for participants who have an observed outcome at 6 months, but are missing the outcome at 12 months, as well as for participants who completed some, but not all, of the questions on the CPG disability score at 12 months. A total of 20 imputations will be performed, and results will be combined using Rubin’s Rules [28]. Only participants included in the analysis will be included in the imputation model. The imputation model will include the three questions that form the CPG disability score at baseline, 6 months, and 12 months, as well as the site of recruitment, age, gender, the HADS depression score at baseline, and employment status (employed or in full-time education versus not employed or in full-time education) (14 variables in total). We chose to include these variables in the imputation model because they will be included in the analysis model (CPG disability score at baseline, 6 months, and 12 months, site of recruitment, age, gender, and HADS depression score at baseline) or because we felt they may be predictive of missingness (employed or in full-time education versus not employed or in full-time education). Imputation will be performed separately within each treatment group [29]. In the intervention group, multilevel imputation will be performed, with 'course’ included in the imputation model as a random effect [30,31].

Missing data in any of the covariates to be adjusted for in the analysis (site of recruitment, age, gender, HADS depression score, CPG disability and baseline) will be accounted for at the same time as missing data in the CPG disability score at 6 or 12 months, as these variables will be included in the same imputation model.

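### Coding each control as a one-person course ties the two arms' total variances together; the type I error drifts modestly from 5% if clustering is material and the arms' variances differ

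*SAP article*

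**What the plan says.** General analysis principles commits the trial to modelling the courses: "All analyses will account for clustering by course in the intervention group". The reason given is that "it is necessary to account for the clustering in the analysis to avoid increasing the type I error rate". For the arm without courses, "Participants in the control group (who do not attend courses), will act as their own cluster". The test level is also set there: "values will be two sided, and the significance level is set at 5" per cent.

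Analysis of primary outcome specifies a linear mixed model with course as a random effect and adds "Restricted maximum likelihood (REML) will be used". The article does not describe the residual variance structure or a degrees-of-freedom method. The same model serves the continuous secondary outcomes, and the Total DDD section specifies one of the same form.

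The imputation is built differently. It is run separately in each arm, with a course random effect in the intervention arm only.

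On size, the Background text after Table 1 gives a plan of "391 in the intervention group and 294 in the control group, to be randomised in a 4:3 ratio". Recruitment then ran on: "This led to 703 participants (403 intervention, 300 control").

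**The concern.** A one-person course cannot separate course variance from residual variance. The 300 controls therefore inform only the sum of the two, and with one residual variance that sum must equal the intervention arm's total. Through this equality the controls influence the estimated course variance, although they attend no course.

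If courses add variance only where courses exist, controls vary less than intervention participants. The constraint then pulls the course variance down and the standard error is too small. If controls vary more, the standard error is too large.

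The article models courses to protect the type I error, so by its own aim the form of the model matters. Whatever error arises enters the primary P value and confidence interval and those of every continuous secondary outcome. The planned sensitivity analyses vary the handling of missing data and the item scoring; none relaxes the constraint. The imputation step does allow the arms to differ in variance, so the analysis model is the stricter of the two.

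**Working it through.** **Inputs from the article.** 403 intervention and 300 control participants; two-sided 5%; singleton controls; REML. The 5% is a setting, so there is no derived figure to reproduce. The stated sizes add up: 391 + 294 = 685, 391/294 = 1.33 (4:3), and 403 + 300 = 703.

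**Assumed, because the article gives none.** Number and size of courses, ICC, and the ratio of control to intervention variance. Covariates and multiple imputation are left out.

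**Step 1: the constraint.** With course variance s and residual variance w, an intervention participant has variance s + w. A control in a course of one also has s + w.

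**Step 2: the bias in the standard error, apart from sampling noise.** Take J = 31 courses of m = 13 (31 × 13 = 403) and set the intervention total variance to 1. The true values are W = 1 − ICC (within course), A = W + 13 × ICC (between-course mean square) and V (control variance). The fitted model has a = w + 13s and t = w + s. In large samples REML settles where this is smallest:

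30(ln a + A/a) + 372(ln w + W/w) + 299(ln t + V/t)

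Here 30 = J − 1, 372 = J(m − 1) and 299 = 300 − 1. The true variance of the difference is A/403 + V/300; the modelled one is a/403 + t/300. With r the ratio of modelled to true standard error, the implied error is 2Φ(−1.96r).

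| ICC | V | A | fitted a, t | true variance | modelled variance | r | implied error |
|---|---|---|---|---|---|---|---|
| any | 1.00 | – | true values | – | – | 1 | 5.0% |
| 0.05 | 0.95 | 1.60 | 1.546, 0.978 | 0.00714 | 0.00710 | 0.997 | 5.1% |
| 0.10 | 0.90 | 2.20 | 2.013, 0.955 | 0.00846 | 0.00818 | 0.983 | 5.4% |
| 0.15 | 0.85 | 2.80 | 2.398, 0.929 | 0.00978 | 0.00905 | 0.962 | 5.9% |
| 0.10 | 1.20 | 2.20 | 2.693, 1.094 | 0.00946 | 0.01033 | 1.045 | 4.1% |

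In the 0.15 row, for example, 2.80/403 + 0.85/300 = 0.00978 and 2.398/403 + 0.929/300 = 0.00905.

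**Step 3: simulation, which adds the uncertainty from few courses.** With 31 × 13 or 25 × 16 courses and 300 controls, the plan's model tested against 1.96 gives:

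- equal totals, or ICC up to 0.05: 4.2-5.8%;
- ICC 0.10, controls less variable: 5.7-6.3%;
- ICC 0.15, controls less variable: 6.1-6.9%;
- ICC 0.10 to 0.15, controls 20% more variable: 3.5-4.7%.

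Arm-specific variances with Satterthwaite degrees of freedom give 4.2-5.3% throughout.

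**Step 4: a wider grid** (50 × 8, 31 × 13 and 20 × 20 courses; 40,000 replicates per scenario; Monte Carlo error about 0.11 points). With equal totals the plan's coding gives 4.6-5.8% for ICC up to 0.20. At ICC up to 0.01 it gives 4.2-5.4% in every scenario. At ICC 0.05 it gives 5.0-6.3% with controls 25% less variable and 3.0-4.7% with controls 50% more variable, so the tolerance at 0.05 presumes moderate variance differences. At ICC 0.20 with controls 25% less variable it gives 6.3-9.1%.

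**Step 5: coding or degrees of freedom?** With 20 × 20 courses, ICC 0.10 and control variance equal to the intervention residual, the plan's coding gives 6.32%, arm-specific variances with 1.96 give 5.79%, and with Satterthwaite 5.13%. So 6.32 − 5.79 = 0.53 points come from the coding and 5.79 − 5.13 = 0.66 from the reference distribution.

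**Step 6: which partially nested model?** With one common residual variance it gives 3.8-7.2% over the grid. It exchanges one constraint for another (control variance = intervention residual) and can do worse than the plan: 5.5-6.0% against 5.2-5.6% with equal totals at ICC 0.10. The arm-specific version gives 4.3-5.3% with Satterthwaite over the whole grid.

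**The case against.** The best case for the plan is that nothing places this trial where harm occurs. If course effects are the only source of extra variance, which is all that the stated reason for modelling clustering implies, control variance equals the intervention residual. On the wider grid the plan's coding then gives 4.6-5.6% for ICC up to 0.05, against 4.5-5.5% for arm-specific variances with the same critical value; at ICC 0.10 it is 5.3-6.3% against 5.2-5.8%. Larger shifts need stronger clustering or another source of unequal variance, and even their direction is unknown. This stands, and it limits the point to a conditional one.

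A reader might infer that the singleton coding takes the primary test off 5% as a matter of course, or that it holds 5% only under equal variances. The article does not support either reading: it has no ICC, course count or arm SDs, and a small ICC is enough to keep the error near 5%. A reader might also infer that any partially nested model is a free cure; Step 6 and the power figures under the fix show otherwise.

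A common residual variance is the default reading, not a statement in the article, and a condensed article may leave the degrees-of-freedom method to the full plan. That also stands: the absence of a df method is not a fault in itself, and the df correction is offered as part of a better model.

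Finally, the adherence-adjusted analysis uses standard errors clustered by course, which do not impose equal variances. But it estimates the effect in compliers, is secondary, and leaves the primary P value and interval as they are.

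**Conclusion.** The constraint follows algebraically from the coding if there is one residual variance. Its consequence is modest and conditional: near 5% when totals are equal or the ICC is up to about 0.05; roughly 6-7% at ICC 0.10 to 0.15 with less variable controls; roughly 3.5-4.5% there with controls 20% more variable. Part of the excess over 5% comes from using 1.96 with few courses. The sizes rest on 25 to 31 assumed courses, assumed ICCs and variance ratios, and models without covariates or imputation. This is a worthwhile, inexpensive improvement to the specification; it is not evidence that the planned test is invalid.

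**What to change.** For the linear mixed models (primary outcome, continuous secondaries, Total DDD), state the variance structure: a course random effect in the intervention arm only, and a separate residual variance for each arm. Use Satterthwaite or Kenward-Roger degrees of freedom, taken as the complete-data degrees of freedom in Rubin's rules where multiple imputation is used. Do not use a common residual variance in the nested model. Leave the logistic and ordered logistic models unchanged: they have no free residual variance, so the remedy does not carry over.

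The change needs SAP wording and a small change to the model code, and no new data. It adds one variance parameter and widens intervals slightly. With 31 × 13 courses, equal totals and a difference of 0.25 SD, power goes from 83.2% to 82.6% at ICC 0.05 and from 76.0% to 75.0% at ICC 0.10, a loss of 0.6 and 1.0 points. If the primary model is to stay as it is, the minimum is to state its residual structure and add the arm-specific model as a sensitivity analysis.

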### Analysis of primary outcome

The primary outcome (CPG disability at 12 months) will be analysed using a mixed-effects linear regression model, with a 'group-based learning course’ as a random effect. Restricted maximum likelihood (REML) will be used. The model will include site of recruitment, age, gender, HADS depression score, and CPG disability at baseline as covariates.

All participants who completed at least one of the three questions that form the CPG disability score at either 6 or 12 months will be included in the analysis. Participants who did not fill out any portion of the CPG disability score at both 6 or 12 months will be excluded from the analysis.

Multiple imputation (MI) [28] will be used to account for participants who have an observed outcome at 6 months, but are missing the outcome at 12 months, as well as for participants who completed some, but not all, of the questions on the CPG disability score at 12 months. A total of 20 imputations will be performed, and results will be combined using Rubin’s Rules [28]. Only participants included in the analysis will be included in the imputation model. The imputation model will include the three questions that form the CPG disability score at baseline, 6 months, and 12 months, as well as the site of recruitment, age, gender, the HADS depression score at baseline, and employment status (employed or in full-time education versus not employed or in full-time education) (14 variables in total). We chose to include these variables in the imputation model because they will be included in the analysis model (CPG disability score at baseline, 6 months, and 12 months, site of recruitment, age, gender, and HADS depression score at baseline) or because we felt they may be predictive of missingness (employed or in full-time education versus not employed or in full-time education). Imputation will be performed separately within each treatment group [29]. In the intervention group, multilevel imputation will be performed, with 'course’ included in the imputation model as a random effect [30,31].

Missing data in any of the covariates to be adjusted for in the analysis (site of recruitment, age, gender, HADS depression score, CPG disability and baseline) will be accounted for at the same time as missing data in the CPG disability score at 6 or 12 months, as these variables will be included in the same imputation model.

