### Sensitivity analyses for primary outcome

#### Method of accounting for missing data

We will perform three sensitivity analyses for the primary outcome to assess the robustness of the results to other methods of account for missing data [32]. The first sensitivity analysis involves specifying a different imputation model than that used in the primary analysis, and the last two sensitivity analyses involve the re-analysis of the primary outcome using two approaches which are not based on MI.

The sensitivity analyses are:

1. We will determine which baseline covariates are associated with loss to follow-up and include them in the imputation model. The analysis model will be the same as that for the primary analysis, except for the inclusion of additional covariates (that is, those that we determined were associated with loss to follow-up) in the imputation model.

2. We will perform a complete case analysis, where all participants who did not complete all components of the CPG disability score at 12 months will be excluded from the analysis. The analysis model will be the same as that for the primary analysis, except missing baseline covariates will be replaced using mean imputation. We used mean imputation as it has been shown to give unbiased estimates and standard errors for the treatment effect in randomised trials, and will suffer only a small loss in efficiency when the amount of missing data is small [33].

3. We will analyse the three components that form the CPG disability score at 12 months, rather than the overall CPG disability score. This will be done by performing a multivariate analysis, where each of the three components from the 12-month score are included in the model as outcomes (that is, each participant will have three outcomes). A three-level mixed-effects model will be used, with random effects for 'course’ and for participant. Treatment-by-question interactions will be included, allowing the treatment effect to vary for each of the three components. An overall treatment effect for CPG disability at 12 months will be estimated using the *lincom* function in Stata (StataCorp, College Station, TX, USA) to combine the treatment estimates from the three separate components. As above, missing baseline covariates will be replaced using mean imputation.

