### Adherence-adjusted analysis

As a secondary analysis, CPG disability, CPG pain intensity, PSEQ, HADS anxiety, HADS depression, CPAQ, HEIQ, and EQ-5D, all at 12 months will be re-analysed to obtain a complier average causal effect of treatment (CACE) [35,36]. This is because while ITT will give an unbiased estimate of the effect of assigning treatment, it may underestimate the effect of actually receiving the treatment. An analysis using CACE will lead to an unbiased estimate of receiving treatment.

We define 'compliers’ as those who attend more than half of the course (that is, those present for at least 12 of the 24 course components). The compliers can only be observed in the intervention group, where an indicator variable will indentify whether the individual complied. The compliers’ class is unobserved in the control group.

The analysis will be performed using the Stata command ivregress, with the option vce (cluster *clustvar*) to account for clustering by course group. Randomisation will be used as an instrumental variable for treatment received. The main analysis will be adjusted for CPG disability score at baseline, site of recruitment, age, gender, and the HADS depression score at baseline. Analyses will be performed using the same multiply imputed datasets as the primary analysis. The assumptions used for this analysis, as well as other adherence-adjusted analyses to be performed, are listed in the online appendix.

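### The intervention-arm imputation model omits course attendance, which may bias the ITT and CACE estimates slightly, most plausibly towards benefit

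*SAP article*

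**What the plan says.** In the SAP article, Analysis of primary outcome, the outcome part of the imputation model is set out first: "The imputation model will include the three questions that form the CPG disability score at baseline, 6 months, and 12 months". The rest follows, "as well as the site of recruitment, age, gender, the HADS depression score at baseline, and employment status", and the list closes with a count: "versus not employed or in full-time education) (14 variables in total". The section justifies each variable either by its place in the analysis model or by its possible value in predicting missingness.

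The arms are handled apart: "Imputation will be performed separately within each treatment group". For the courses, "In the intervention group, multilevel imputation will be performed", with course as a random effect. The values to be filled in belong to "participants who have an observed outcome at 6 months, but are missing the outcome at 12 months" and to people who answered only part of the 12-month score. Those with no CPG disability item at either time point are left out of both the analysis and the imputation.

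Under Method of accounting for missing data, the only alternative imputation model is described as follows: "We will determine which baseline covariates are associated with loss to follow-up and include them in the imputation model".

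Under Adherence-adjusted analysis, a complier is someone present for 12 or more of 24 components. This is observed in the intervention arm only, and randomisation is the instrument for treatment received. On the data: "Analyses will be performed using the same multiply imputed datasets as the primary analysis". That section refers the assumptions and further adherence-adjusted analyses to an online appendix.

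**The concern.** An imputation model should contain the variables of the analysis model it feeds, plus variables related to both missingness and outcome. Attendance is the exposure in the CACE model, and staying away from the course may well go with not returning a questionnaire. With attendance omitted, a non-attender who lacks the 12-month score receives a draw that takes no account of non-attendance, except so far as the person's own answers already reflect it.

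Controls have no course to miss, so any distortion from this source falls on one arm and passes into the treatment contrast. The primary ITT estimate is exposed, and so are the CACE estimates, planned for eight outcomes at 12 months. The plan says the CACE analysis gives an unbiased estimate of the effect of receiving treatment; with these datasets that also requires missingness to be unrelated to attendance given the listed variables, or attendance to be unrelated to the outcome given them.

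**Working it through.** **1. The plan's own count.** 3 questions x 3 time points = 9. Site, age, gender, baseline HADS depression and employment = 5. 9 + 5 = 14, as stated. Attendance is absent.

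**2. Does anything else carry it?** The course random effect records which course a person belongs to, not whether they came. The first missing-data sensitivity analysis admits baseline covariates only. The second and third do not use multiple imputation, and neither includes attendance. The missing-not-at-random scenarios concern people excluded for having no follow-up, not people whose 12-month score is imputed.

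**3. Size of the bias.** All inputs here are assumptions: SD 25, correlation 0.6 between baseline and each follow-up, and 0.65 between 6 and 12 months. Let M be the share of the intervention arm missing at 12 months; p_obs and p_mis the shares of non-attenders among the observed and the missing; G12 and G6 the non-attender minus attender difference in mean score at 12 and 6 months; and b the slope of the 12-month on the 6-month score given baseline. With attendance omitted:

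ITT bias = M x (p_obs - p_mis) x (G12 - b x G6); CACE bias = ITT bias / share attending.

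Moderate case: 30% non-attenders, missing 8% of attenders and 20% of non-attenders, effect -10 in attenders at both times (so G12 = G6 = 10).

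- M = 0.7 x 0.08 + 0.3 x 0.20 = 0.116
- p_obs = 0.3 x 0.80 / 0.884 = 0.271; p_mis = 0.06 / 0.116 = 0.517
- Ignoring the 6-month score: 0.116 x (0.271 - 0.517) x 10 = -0.285
- b = [(0.65 - 0.36) x 625 + 0.271 x 0.729 x 100] / [(1 - 0.36) x 625 + 0.271 x 0.729 x 100] = (181.25 + 19.8) / (400 + 19.8) = 0.479
- With the 6-month score: -0.285 x (1 - 0.479) = -0.149; CACE: -0.149 / 0.7 = -0.21

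A simulation of 2,000,000 intervention-arm records with regression imputation gave -0.153 and -0.218, which agrees within simulation error. With attendance added, both became 0.00. The 6-month score alone removes about half of the bias.

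**4. Range** (same simulation, attendance omitted; negative means benefit overstated):

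| Non-attenders | Missing, attenders / non-attenders | Effect in attenders, 12 / 6 months | True ITT | ITT bias | CACE bias |
|---|---|---|---|---|---|
| 30% | 8% / 8% | -10 / -10 | -7.0 | 0.000 | 0.000 |
| 30% | 8% / 20% | 0 / 0 | 0.0 | -0.004 | -0.006 |
| 30% | 8% / 20% | -10 / -10 | -7.0 | -0.153 | -0.218 |
| 30% | 8% / 20% | -10 / -5 | -7.0 | -0.223 | -0.319 |
| 30% | 5% / 30% | -10 / -10 | -7.0 | -0.317 | -0.452 |
| 40% | 5% / 40% | -10 / -10 | -6.0 | -0.535 | -0.891 |
| 40% | 5% / 40% | -10 / 0 | -6.0 | -1.040 | -1.734 |
| 40%, untreated score 15 points lower (better) | 5% / 40% | -5 / -5 | -3.0 | +0.538 | +0.897 |
| 30% | 20% / 8% | -10 / -10 | -7.0 | +0.157 | +0.225 |

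A second simulation used other assumptions: 65% compliers, effect -6 in compliers, compliers 5 points better untreated, SD 25, missing 8% of compliers, 35% of non-compliers and 12% of controls, all with a 6-month score. It gave ITT -4.07 against a true -3.9, and CACE -6.27 against -6.0. With attendance added it gave -3.84 and -5.91, so simulation noise is roughly 0.06 to 0.09.

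**5. Scale.** With SD 25 and the 403 and 300 randomised, the unadjusted standard error is 25 x sqrt(1/403 + 1/300) = 1.91, ignoring clustering, loss and covariate adjustment. A bias of 0.15 is 0.15 / 1.91 = 0.08 standard errors; a bias of 1.04 is 0.54.

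**The case against.** The case for leaving the plan alone is a fair one. Attendance is not in the primary analysis model, so for the ITT estimate the plan's rule calls for it only if it predicts missingness, and the document gives no evidence that it does. The 6-month answers postdate the course and already absorb part of any attendance effect. The CACE bias is the ITT bias rescaled, not a second defect. The appendix on adherence-adjusted analyses is not shown and may deal with the CACE part. All of this stands. It limits the size and certainty of the point but does not remove it: for the CACE analysis, attendance is a variable of the analysis model, and the primary imputation list is explicit and closed.

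Two stronger readings are tempting, and the document supports neither.

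- A reader might infer that missing scores of non-attenders are filled in from attenders, so that benefit is necessarily overstated. In fact the model is fitted to the whole intervention arm, including non-attenders with observed scores, and conditions on the person's own baseline and 6-month or partial 12-month items. The table shows zero bias when either dependence is absent and a reversed sign in two cases.
- A reader might also charge losses without any follow-up to the imputation model. If half of those missing in the second simulation have no follow-up and are excluded, the ITT estimate is -4.38, an error of 0.48 (12% of 3.9); related scenarios gave 0.26 to 0.88. But adding attendance moves -4.38 only to -4.25, which is 0.13 of 0.48, or about 27%. The rest comes from the exclusion rule, a separate matter that the plan takes up under Participants with no completed follow-ups. Those figures should not be attributed to the imputation model.

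**Conclusion.** The omission is real, and no planned multiple-imputation analysis tests it. It matters only if 12-month missingness and the 12-month score both depend on attendance after the listed variables, including the 6-month items, are taken into account. If non-attenders do worse and are lost more often, which is the most plausible pattern but not one the document establishes, both estimates lean towards benefit. Under the assumed inputs the ITT bias is mostly a few tenths of a point and reaches about 1 point with 40% non-attenders, 40% of them missing and no benefit yet at 6 months. The matching CACE figures are larger by one over the share complying. Attendance rate, missingness by attendance, SD and correlations are all assumed. This is a modest, inexpensive improvement that makes the missing-at-random assumption more credible; it does not show that the primary result would be wrong.

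**What to change.** Add attendance, as the number of the 24 components attended or at least the complier indicator, to the intervention-arm imputation model for CPG disability and for the outcomes that use the same strategy. As a minimum, use this model for the datasets that feed the CACE analyses and report it as a sensitivity analysis for the ITT estimate. Because the arms are imputed separately, the absence of attendance in controls is no obstacle. Its being measured after randomisation is none either, since the 6-month items already in the model are too. State in the main text whether the online appendix covers the CACE part.

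The cost is one sentence and one further variable in one arm (15 instead of 14 for the primary outcome). Attendance is already needed to define compliers, so no data are added. The downsides are slightly more complex imputation code and possibly a slightly less favourable estimate.
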